# Impact of mhealth messages and environmental cues on hand hygiene practice among healthcare workers in the greater Kampala metropolitan area, Uganda: study protocol for a cluster randomized trial

**DOI:** 10.1186/s12913-021-06082-3

**Published:** 2021-01-26

**Keywords:** Hand hygiene, Healthcare workers, Hand hygiene interventions, Behaviour centred design, Uganda

## Abstract

**Background:**

Hand hygiene (HH) among healthcare workers (HCWs) is critical for infection prevention and control (IPC) in healthcare facilities (HCFs). Nonetheless, it remains a challenge in HCFs, largely due to lack of high-impact and efficacious interventions. Environmental cues and mobile phone health messaging (mhealth) have the potential to improve HH compliance among HCWs, however, these remain under-studied. Our study will determine the impact of mhealth hygiene messages and environmental cues on HH practice among HCWs in the Greater Kampala Metropolitan Area (GKMA).

**Methods:**

The study is a cluster-randomized trial, which will be guided by the behaviour centred design model and theory for behaviour change. During the formative phase, we shall conduct 30 key informants’ interviews and 30 semi-structured interviews to explore the barriers and facilitators to HCWs’ HH practice. Besides, observations of HH facilities in 100 HCFs will be conducted. Findings from the formative phase will guide the intervention design during a stakeholders’ insight workshop.

The intervention will be implemented for a period of 4 months in 30 HCFs, with a sample of 450 HCWs who work in maternity and children’s wards. HCFs in the control arm will receive innovatively designed HH facilities and supplies. HCWs in the intervention arm, in addition to the HH facilities and supplies, will receive environmental cues and mhealth messages. The main outcome will be the proportion of utilized HH opportunities out of the 9000 HH opportunities to be observed. The secondary outcome will be *E. coli* concentration levels in 100mls of hand rinsates from HCWs, an indicator of recent fecal contamination and HH failure. We shall run multivariable logistic regression under the generalized estimating equations (GEE) framework to account for the dependence of HH on the intervention.

**Discussion:**

The study will provide critical findings on barriers and facilitators to HH practice among HCWs, and the impact of environmental cues and mhealth messages on HCWs’ HH practice.

**Trial registration:**

ISRCTN Registry with number ISRCTN98148144. The trial was registered on 23/11/2020.

**Supplementary Information:**

The online version contains supplementary material available at 10.1186/s12913-021-06082-3.

## Background

Adequate water, sanitation and hygiene (WASH) is critical in the provision of quality health care in healthcare facilities (HCFs). Improved WASH infrastructure and practices in HCFs can significantly reduce the risk of healthcare acquired infections (HCAIs). Moreover, it increases trust and uptake of healthcare service while increasing efficiency and improved staff morale. In addition, all major initiatives to improve global health largely depend on basic WASH services in HCFs [1]. Despite this, many HCFs in low- and middle-income countries (LMICs) lack basic WASH infrastructure and where it exists the coverage is low. The recent Joint Monitoring Programme (JMP) report on WASH in HCFs indicates that approximately 14% of HCFs had limited water services while 21 and 16% respectively had no sanitation and hygiene services, impacting nearly 2 billion people [2]. The lack of WASH infrastructure compromises the ability to provide safe and quality healthcare services, and places both healthcare workers (HCWs) and patients at a considerable and yet preventable health risk of HCAIs. Indeed there is a strong biological plausibility that pathogens responsible for HCAIs are more prevalent in facilities with substandard WASH services [3], and mothers and neonates are at the greatest risk of getting exposed to HCAIs [4–6].

Hand hygiene, a critical component of standard infection prevention and control (IPC), is a leading simple, crucial and inexpensive measure for preventing HCAIs [7–9]. However, there is limited evidence on efficacious interventions that have the potential to increase hand hygiene compliance in HCFs [10, 11]. Yet, hand hygiene compliance among HCWs in HCFs remains low especially in low and middle income settings [10, 11]. There is an avalanche of reasons for suboptimal hand hygiene practices and these defer by settings and resources available. For example lack of appropriate infrastructure and equipment [12]. Other factors for poor hand hygiene compliance include belonging to a certain professional category, working in certain departments, understaffing and wearing gloves and gowns [13]. The barriers are not any different in Uganda, where low compliance to hand hygiene among HCWs has been related to lack of knowledge of the transmission risk, and limited hand hygiene infrastructure and supplies [14, 15].

In Uganda, most of the existing research on WASH in HCFs has mainly focused on assessing WASH status [14–17] but there has been generally a lack of understanding of the barriers and facilitators to hand hygiene among HCWs, and research on simple, effective and inexpensive interventions to enhance hand-hygiene practices among HCWs is limited. In other settings, previous studies have shown that the use of mobile phone technology in health messaging (mhealth) has great potential to promote health care including improving HCWs’ adherence to standard guidelines [18, 19]. There is growing evidence that mhealth interventions are critical in improving patients’ adherence to treatment as well as adherence of HCWs to treatment guidelines. Despite the impact of mHealth in HCWs’ adherence, there is limited evidence about the use and effect of the mhealth in enhancing compliance to WASH practices including hand hygiene among HCWs [20, 21]. In addition, there is also evidence that nudges (environmental cues) in schools, have the potential to improve handwashing with soap among school-aged children [22], however, such evidence is limited for HCFs. Complex interventions such as use of HCF wide poster campaign, combined with performance feedback and alcohol-based hand rub (ABHR) placed at every bedside; introducing ABHR accompanied by education/training; applying social marketing strategies as well as using multiple strategies including involvement of staff in planning activities have been suggested as interventions for improving adherence to hand-hygiene guidelines among HCWs [23]. However, there is limited evidence on the effect of simple inexpensive mhealth and nudges/environmental cues related interventions on compliance to hand hygiene among HCWs.

### Study objectives

#### General objective

To determine the impact of mobile phone WASH text messages and environmental cues on hand hygiene practice among HCWs in the Greater Kampala Metropolitan Area (GKMA).

#### Specific objectives

To explore the facilitators of hand hygiene among HCWs in HCFs in the GKMA.To explore the barriers to hand hygiene among HCWs in HCFs in the GKMA.To determine the impact of mhealth messages and environmental cues on hand hygiene practices among HCWs in HCFs in the GKMA.

## Methods

### Study setting

The study will be conducted in the GKMA which includes Kampala, Wakiso and Mukono districts. According to the Uganda Bureau of Statistics (UBOS), Kampala has a day time population of approximately 4 million people and a night time population of approximately 1.5 million [24]. The rate of urbanisation in Kampala and the neighbouring districts of Wakiso and Mukono is so high, and these areas are experiencing many urban challenges including growth of slums, which are characterized by poverty, poor living conditions and limited access to various services [25, 26]. In partnership with the Ministry of Health (MOH), Ministry of Water and Environment (MWE), WaterAid Uganda and Kampala Capital City Authority (KCCA), we recently conducted a WASH assessment in 63 HCFs in the GKMA, which indicated significant gaps in WASH [16]. This proposed study will be building upon the evidence from that assessment, as well as priorities and needs that have been identified by stakeholders. The intervention will be premised on the understanding that mobile phone usage is very high among HCWs. Indeed, according to the Uganda National Information Technology Agency (NITA), 70.9% of adult Ugandans own a mobile phone, and ownership is even higher in professional groups of people including HCWs [27]. As of 2018, the number of Government and Private not for Profit (PNFP) HCFs in the 3 districts of the GKMA is as provided in Table 1 [28].

**Table 1 Tab1:** Number of HCFs in Kampala, Wakiso and Mukono districts

District	Hospitals		HC IVs		HC IIIs		Total
	Government	NGO	Government	NGO	Government	NGO	
Kampala	5	9	4	3	8	12	41
Mukono	0	1	2	1	13	1	18
Wakiso	1	3	5	0	21	16	46
TOTAL	6	13	11	4	42	29	105

### Study design

In Uganda, the healthcare system is organised into a four-tier system with hospitals and health centres (HCs) of levels IV, III and II [29]. General hospitals (catchment population 500,000 people) provide preventive, promotive, curative, maternity, and inpatient health services and surgery, blood transfusion, laboratory, and medical imaging services. HC IVs have a target population of 100,000 people and are responsible for preventive, outpatient health services, maternity, inpatient health services, emergency surgery and blood transfusion, and laboratory services. HC IVs provide all the services of HC IIIs except emergency surgery. The study will be carried out in public HCs of level III and IV in Wakiso and Mukono districts, using a cluster-randomized trial (CRT) design. The study will be restricted to public HC IVs and IIIs because these offer affordable Maternal, New-born and Child Health (MNCH) services to the majority of the population in the GKMA [14], and only HCFs in Wakiso and Mukono will be studied since they are likely to have similar characteristics as they are more rural and receive less funding compared to those in Kampala. The intervention will be preceded by a formative study which will be conducted in the Kampala, Mukono and Wakiso districts. The reason for focusing on HCFs and departments that offer MNCH services is because mothers and neonates are at a greater risk of getting exposed to HCAIs [4–6], and there is therefore critical need to improve the status of WASH in maternal and children’s wards.

The study will be guided by the “Behaviour Centred Design (BCD)” model and theory for behaviour change [30], which guides hand hygiene program design through the “ABCDE” (Assess, Build, Create, Deliver and Evaluate) steps (Fig. 1). The model provides the BCD process on the outside and the theory of change on the inside. The theory suggests that, the right behavioral response depends on the behavior settings (physical, social and temporal context) in which individuals find themselves [31], and that three causal links must be made: from the environment (modified by an intervention) to psychological change in the target population (body and brain), to performance of the target behaviors (which results in changes to the state-of-the-world).

**Fig. 1 Fig1:**
[figure not shown]
Study steps adapted from the Behaviour Centred Design model for behaviour change [30]

Prior to the implementation of the CRT, the investigators will obtain a list of HCFs and healthcare providers from the respective district health offices. This list will be used to randomly assign the clusters (HCFs) to the intervention and control groups. Once the clusters have been assigned, the study participants in the maternal and children’s wards within the selected HCFs will be informed about the purpose of the study and recruited in the study after the consenting process.

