The mhealth messages will be sent to study participants using either short message service (sms) or whataspp, depending on the decision of the stakeholders in the stakeholders’ workshop. In case stakeholders choose using the sms option, messages will be sent to participants using RapidSMS, which is a free and open-source framework for dynamic data collection, logistics coordination and communication. The service will enable a two-way communication between HCWs using basic SMS mobile phone technology. RapidSMS will be installed on a secure Linux server running Ubuntu 18.04.5 LTS with the following hardware specifications: (1) Intel Core i7-8700T 2.40 GHz processor with 16.0 GB of RAM, and (2) An MTCBA-GF4 modem attached via a serial interface. RapidSMS dependences that include Python and Django web framework will also be installed on the same machine. For compatibility, we shall install Python 3.7.3 and Django 2.2. For communication between the modem and RapidSMS, we shall install Kannel, which is a free and open source SMS gateway compatible with RapidSMS. With Kannel’s SMS Delivery Report functionality, we shall be able to track the status of messages sent to HCWs. We shall configure the system to automatically send mhealth messages to HCWs at specific weekly intervals. Our server will enable HCWs to respond to the messages sent by the system. SMS received by the system from HCWs will be toll free thus HCWs will not incur any costs when responding to mhealth messages. Responses from HCWs will be securely stored in MySQL database on the server; this will enable further analytics on the data. Authorized access to the data will be available via secure login into the system. The data will be available and downloadable in CSV format to enable further processing by third party statistical tools. The software can track message history and delivery, and this will be critical in understanding the proportion of HCWs receiving and responding to sms messages on a daily basis.
iii.Randomization and Trial arms

Using a list of level III and IV HCFs in the study districts [28], the project coordinator will use computer-generated random numbers to assign HCFs to the intervention and control arms. All HCWs from the same HCF will be allocated to the same group as the randomized HCF in which they are working. HCWs will be enrolled by research assistants (RAs) under the guidance of the principal investigator, and they will be masked off the intervention they are receiving.

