iv.Masking/ blinding

The data analysts and the data collectors will be blinded to the group assignment. In order to achieve blinding for the data collection team, independent teams will collect data from either arm of the trial. In addition, data collectors will be trained separately.
xxii.Inclusion and exclusion criteria

The study will enrol participants working in the maternal and pediatric wards of selected HCFs, and Table 2 summarizes the inclusion and exclusion criteria.
vi.Intervention monitoring

**Table 2 Tab2:** Inclusion and exclusion criteria

Inclusion criteria	Exclusion criteria
• Age of 18 and above • Both male and female • Minimum of six months experience at the HCF. • HCWs with appointment letters to work at the selected HCF • Full-time staff at the selected HCF • Informed written consent to participate in the study	• All HCWs in maternal and children’s wards of selected HCFs, who will be on leave at the time of the baseline • All HCWs workers in maternal and children’s wards of selected HCFs, who will be so sick at the time of the baseline • Refusal to give informed written consent to participate in the study.

For quality delivery of the intervention and ensuring that results are acceptable to the different stakeholders, an intervention support team will be in place to provide technical guidance and support. The intervention support team or data monitoring committee (DMC) will be comprised of 6 members, with a representative from the Environmental Health Department at the MOH, KCCA Public Health department, MWE, NGOs, HCFs and private sector. The independent DMC will be chaired by a representative from the Environmental Health division at the MOH.

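### Facilities are allocated before healthcare workers are recruited and, by inference, before baseline, so enrolment and baseline measurements can differ by arm

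*Protocol article*

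**What the plan says.** **Order.** Under Study design (text after Fig. 1), the investigators obtain a list of facilities and providers from the district health offices. "This list will be used to randomly assign the clusters (HCFs) to the intervention and control groups". The next sentence begins "Once the clusters have been assigned, the study participants in the maternal and" and ends with these people being "recruited in the study after the consenting process".

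**Who does what.** Under Delivery of the intervention, item iii, "the project coordinator will use computer-generated random numbers to assign HCFs to the intervention and control arms", and "HCWs will be enrolled by research assistants (RAs) under the guidance of the principal investigator". The same sentence says that participants are masked to what they receive.

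**Data teams.** Item iv says that data collectors are blinded, and that to achieve this "independent teams will collect data from either arm of the trial". The teams are also trained separately.

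**Eligibility.** Table 2 excludes ward staff "who will be on leave at the time of the baseline" and those too sick at that time.

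**Numbers.** The sample size text sets 15 facilities per arm, with 15 HCWs in each: a target of 13 nurses or midwives and 2 doctors or clinical officers. It gives no rule for picking them.

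**Sampling frame.** The trial is limited to public level III and IV health centres in Wakiso and Mukono. Table 1 gives their numbers; the Mukono row reads "Mukono 0 1 2 1 13 1 18".

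**The concern.** Cluster randomisation makes the two groups of facilities comparable. It does not do the same for people who are approached after the arms are fixed. If those who invite staff know the arm, the choice of whom to approach, how the study is explained and who agrees can all vary with it. Exclusions applied at baseline, such as leave and sickness, then also fall after allocation.

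Baseline hand hygiene is observed behaviour, and the article itself expects social desirability to affect such observation. A baseline taken after allocation is no longer certain to be free of the arm, so it is a weaker reference point for judging change. Analysis cannot reliably undo differential enrolment, because the reasons for entering are not recorded.

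**Working it through.** **1. Is allocation before recruitment stated or inferred?** Stated. The Study design section puts assignment first, and information, consent and recruitment second.

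**2. Is baseline after allocation stated or inferred?** Inferred, but firmly.
- The Evaluation section surveys participating HCWs at baseline, so they have been recruited, and recruitment follows assignment.
- Data teams are split by arm (item iv), with no exception for baseline. Teams can be split this way only once the arms are known.
- Fig. 2, which shows timing, is not available to check this.

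**3. Do the stated safeguards fix who is enrolled before allocation?**
- *Provider list.* It is obtained before assignment, but the text uses it for assigning facilities and does not say that it settles which HCWs enter.
- *Eligibility criteria.* Most are objective (appointment letter, full-time post, six months at the facility). Consent, leave and sickness are still resolved after allocation.
- *Quota of 13 and 2.* It fixes how many of each cadre, not which individuals.
- *Masking of participants.* It does not cover those who recruit. It is also hard to sustain with messages that invite replies and visible cues.
- *Blinding of data collectors.* It is sought through arm-specific teams, which requires the allocation to be in operational use. If the split applies at baseline, team and arm also cannot be separated there.

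None of these closes the gap.

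**4. Size of any bias.** It would depend on the share of enrolment altered by knowledge of the arm and on how far those HCWs differ in compliance. The documents give neither, so no figure is offered.

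**5. Secondary: chance imbalance in facility level.** Inputs from the Government columns of Table 1: Mukono 2 level IV and 13 level III; Wakiso 5 level IV and 21 level III.

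Frame: 2 + 13 + 5 + 21 = 41, of which 2 + 5 = 7 are level IV and 13 + 21 = 34 are level III. Expected level IV among 30 drawn at random: 7 × 30/41 = 5.1.

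Assume a simple 15:15 draw. With m level IV facilities among the 30, the chance that k fall in one arm is C(15,k) × C(15,m−k) / C(30,m). The chance that the arms differ by 3 or more is 1 minus the chance of the closer splits:

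| m | Chance of closer splits | Difference ≥ 3 |
|---|---|---|
| 4 | (105² + 2×455×15)/27,405 = 0.900 | 10.0% |
| 5 | 2×455×105/142,506 = 0.670 | 33.0% |
| 6 | (455² + 2×1,365×105)/593,775 = 0.831 | 16.9% |
| 7 | 2×1,365×455/2,035,800 = 0.610 | 39.0% |

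Odd values of m give higher figures because an even split is impossible.

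If the 30 are a random draw from the 41, the chances of m = 3, 4, 5, 6 and 7 are 0.060, 0.201, 0.349, 0.291 and 0.091. For m = 3 a difference of 3 has chance 2×455/4,060 = 0.224; for m below 3 it cannot occur. The weighted sum is 0.013 + 0.020 + 0.115 + 0.049 + 0.035 = 0.233, or about 23%.

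With allocation stratified by level, the difference is 0 or 1 (for example 4 against 3), so the chance of 3 or more is 0. The planned 450 HCWs in 30 clusters do not change.

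**The case against.** The best defence is that the room for selection may be small. Eligibility is largely objective, the cadre quota is fixed, a provider list exists beforehand, and enrolment is by research assistants rather than by the coordinator who allocates. Nothing says that the assistants are told the arm. If a ward has barely 15 eligible staff, there is little to choose from. This limits the likely size of the problem, but the number of eligible staff per facility is not given, so it does not remove it.

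Four stronger readings are tempting and are not supported.

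- *The allocation is unstratified.* The article names computer-generated random numbers and no strata, but it is a condensed text and silence is not a denial. The imbalance figures are therefore conditional on a simple draw.
- *Imbalance in facility level is bias.* It is chance variation under a valid randomisation. The article argues that the chosen facilities are likely to be similar, gives hand hygiene supplies to both arms and plans a multivariable model. No document figure shows that compliance differs by level.
- *The analysis adjusts for a contaminated baseline.* The Data analysis section mentions other covariates without naming baseline hand hygiene, so this cannot be asserted.
- *Reversing the order costs nothing.* It is free in sample size but not in logistics.

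**Conclusion.** The point holds for the sequence. The plan explicitly assigns facilities before HCWs are approached, and baseline after allocation is a firm inference. With no selection rule for the 15 HCWs and data teams split by arm, enrolment and baseline can differ by arm for reasons other than chance. That recruiters know the arm is a possibility that the plan leaves open, not something it states. The size of any bias cannot be derived, and a reader should not attach a number of percentage points to it.

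Stratification is a lesser matter of efficiency. If the draw is simple, the chance of a difference of 3 or more in level IV facilities is 10% to 39% for 4 to 7 of them among the 30, and about 23% on average. This assumes that the 30 come from the 41 public facilities in Table 1.

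The sequence should be changed before recruitment. The Trial status section places the study in its formative phase, so this was still feasible when the article was written.

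**What to change.** 1. In all 30 facilities, list the eligible HCWs, state how the 15 are chosen, then consent and enrol them.
2. Complete baseline observations and hand rinsates everywhere with common teams.
3. Only then release the allocation, generated by someone with no part in recruitment.
4. Correct the Study design text and item iii to this order, and state in item iv that the arm-specific teams do not apply at baseline.
5. As an efficiency gain, draw the allocation within strata of facility level, and of district if strata sizes allow (Mukono has only 2 public level IV centres). Include the strata in the generalised estimating equations model. If the full protocol already stratifies, say so in one line.

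**Cost.** No added sample size. No facility can start the intervention until baseline is finished in all 30, and arm-specific teams cannot be used at baseline. Stratification needs a small change to the randomisation program.
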